### Sample size

For the sample size determination, the estimated occurrence over one year of the composite clinical endpoint of cardiac death, MI, resuscitated cardiac arrest and cardiac re-hospitalization (WHF, ACS, arrhythmia) for PET is 27% and for standard care is 40%, based on the Ottawa-FIVE substudy [28] of the PARR-2 [27] study in which the composite event rates were 19% and 41%, respectively. These estimates were considered reasonable as it reflects the outcome rates that may be achievable at a facility with expertise and access to FDG PET imaging. There are no similar data upon which to draw an estimate for CMR. Considering the Schinkel *et al*. publication [38], which noted sensitivity of CMR to be between PET and standard care modalities and based on expert consensus from our IMAGE-HF workshop (16 December 2008 in Toronto, Canada), we estimate the event rate for CMR directed care would lie between the above values at 34%. Hence, an overall rate for the alternative (PET, CMR) modalities would be approximately 30%. The rates are considered conservative since the mean duration of follow-up will be 2 years, whereas the PARR-2 study was 1 year.

For the primary hypothesis, using the two-sided log-rank test for comparing advanced (PET + CMR) versus standard modalities with a 2:1 patient allocation, a sample size of 495 patients (of which 330 are allocated to the advance modality and 165 are allocated to the standard modality) would be needed in order to detect a difference after 1 year in the composite clinical endpoint of 30% for the advanced modalities (PET, CMR) compared to 40% for standard care modalities (SPECT). This is calculated with a level of significance of 0.05 and power of 80%, and assuming a uniform accrual of patients over the 2.5 year recruitment period, a 1 year minimum follow-up period and a 10% loss from each study group. The difference of 10% was considered to be a minimal clinically important difference based on a consensus of the IMAGE-HF investigators.

For the secondary hypothesis, using the Cox regression model for comparing the advanced modalities PET versus CMR with an approximate 1:1 patient allocation, a sample size of 548 patients per modality is needed considering an anticipated rate for the composite clinical endpoint of 30% after 1 year, a level of significance of 0.05, a power of 80% and a loss to follow-up of 10%. The sample size calculation is complicated by the fact that 766 patients (383 per group) from the registry (in which patients in the registries were clinically directed to PET or CMR) will be combined in the analysis with the 330 patients (165 per group) from the randomized part of the study (in which patients in the randomized study will be randomly allocated to PET versus CMR versus standard modality) for a total of 1096 patients (548 per group). For a sample of 1096 patients, a Cox regression of the log hazard ratio of the composite clinical endpoint on the group allocation variable (PET versus CMR) with a conservative standard deviation of 0.5 (based on an approximate equal allocation to PET and CMR), achieves 80% power at a 0.05 significance level to detect a 40% increase in the hazard ratio to1.4. This increase in the hazard ratio was deemed to be the minimal clinically important difference based on a consensus among the IMAGE-HF investigators. The sample size includes an adjustment to accommodate confounding by indication for allocation patients to PET versus CMR by incorporating a multiple regression of the group allocation variable on the other covariates in the Cox regression model; a conservative estimate of this confounding was considered by taking a value of 0.25 for the multiple correlation coefficient R for the relationship between the group allocation variable and the set of covariates identified.

The total sample size is thus 1,096 + 165 = 1,261.

### Statistical analysis

Descriptive statistics will be used to summarize the characteristics of the patients for each imaging technology on demographic, clinical and site-related factors, and differences between these groups will be reviewed for their clinical significance.

#### Analysis populations

For the purposes of data analysis, three study populations will be considered: Intent-to-treat (ITT) Population, As-Treated Population and Per-protocol Population. The ITT population will be used for the main analysis for all primary and secondary objectives, except for the safety analysis where the as-treated population will be used. As a secondary analysis, the analyses will be repeated for the as-treated and per-protocol populations.

#### Primary analysis (advanced versus standard imaging)

For the primary analysis, the time-to-event of the composite clinical endpoint of cardiac death, MI, arrest and cardiac re-hospitalization (WHF, ACS, arrhythmia) will be compared between the advanced modality (PET or CMR) to an approach with standard care using SPECT imaging using survival analysis. Kaplan-Meier survival curves of the primary endpoint will be compared between the advanced and standard modalities with the log-rank test. Potential confounding variables of the relationship between the imaging technologies and the primary endpoint will be assessed. In particular, propensity scores based on patient factors (for example, in/outpatient, NYHA class, HF duration, diabetes, atrial fibrillation) and site factors (for example, time-to-imaging, time-to-therapy) will be used in the analysis if necessary to adjust for potential differences. A Cox proportional hazard models will be used to assess the occurrence of the endpoints between the imaging technologies (model will include a group indicator variable) adjusting for any pertinent baseline differences identified. The proportional hazards assumption underlying the Cox model will be assessed.

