### Study hypotheses and objectives

#### Primary hypothesis

In patients with HF due to IHD with left ventricular ejection fraction (LVEF) ≤ 45%, a management algorithm that applies alternative imaging strategies (PET or CMR) achieves a better clinical outcome measured as the composite clinical endpoint of cardiac death, MI, resuscitated cardiac arrest and cardiac re-hospitalization (hospitalization due to heart failure, acute coronary syndrome or arrhythmia) than an approach with standard care using SPECT imaging.

Secondary hypotheses

1) Compared to standard care, in patients with HF due to IHD with LVEF ≤45% a management algorithm that applies alternative imaging modalities (PET or CMR) achieves: a) more efficient use of revascularization procedures with similar complication rates than standard care imaging strategies; b) better HF and angina symptom reduction; c) better quality of life (QoL), measured using MLHFQ and EQ5D; and d) is cost-effective.

2) In patients with HF due to IHD with LVEF ≤45%, a HF management algorithm that applies PET achieves a better primary (composite clinical endpoint) and secondary outcomes (revascularizations, remodeling, QoL, cost effectiveness) compared to one that applies CMR.

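### Kaplan-Meier curves for a composite that counts only cardiac death will overstate event risks in both arms; cumulative incidence curves would not, and the primary test is unaffected

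*Protocol article*

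**What the plan says.** The Primary hypothesis defines the outcome as the "composite clinical endpoint of cardiac death, MI, resuscitated cardiac arrest and cardiac re-hospitalization". The objectives, the Sample size section and the primary analysis section likewise include cardiac death and no other death.

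For this endpoint the section on the primary analysis (advanced versus standard imaging) specifies that "Kaplan-Meier survival curves of the primary endpoint will be compared between the advanced and standard modalities with the log-rank test". It adds an adjusted analysis: "A Cox proportional hazard models will be used to assess the occurrence of the endpoints between the imaging technologies".

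The article does not say how a non-cardiac death before a first event is handled, and it names no competing-risk method. The Missing data section covers missing values only.

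**The concern.** A patient who dies of a non-cardiac cause can no longer have a first event of this composite. Ordinary Kaplan-Meier estimation has no place for that outcome except as censoring. It then treats the patient as still able to have the event later, at the same rate as those who remain under observation. For a death that is false.

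The curves would therefore not show the proportion of patients who actually have an event by a given time. They would show a higher figure, and the gap would widen with follow-up. At stake are the absolute risks that a reader takes from the main figure of a trial intended to inform decisions on investment in imaging. The comparison of the arms is not at stake.

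**Working it through.** **Inputs from the Sample size section**
- 1-year event rates: 40% standard, 30% advanced.
- Test and allocation: "using the two-sided log-rank test for comparing advanced (PET + CMR) versus standard modalities with a 2:1 patient allocation"; level 0.05, power 80%.
- Timing and loss: "uniform accrual of patients over the 2.5 year recruitment period, a 1 year minimum follow-up period and a 10% loss from each study group".

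**Input not in the documents**
- The non-cardiac death hazard m. I assume it constant, equal in the two arms, and between 1% and 5% per year.

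**Step 1: hazards.** With exponential event times, the standard hazard is −ln(0.6) = 0.511 per year and the advanced hazard is −ln(0.7) = 0.357 per year. The hazard ratio is 0.357/0.511 = 0.698.

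**Step 2: the plan's own figure.** The Lachin-Foulkes formula with these hazards and the stated design gives 496 patients with exponential loss of 10% per year. Without loss it gives 448.9, and 448.9/0.9 = 498.7. The plan states 495. The figure reproduces closely, so these hazards are a fair basis for what follows and the sample size is not in dispute.

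**Step 3: the two estimands.** With event hazard l and non-cardiac death hazard m, at time t:
- 1 minus Kaplan-Meier, non-cardiac deaths censored: 1 − exp(−l·t)
- Cumulative incidence (what Aalen-Johansen estimates): l/(l+m) × [1 − exp(−(l+m)·t)]

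The first exceeds the second whenever m > 0. The direction does not depend on the assumed rate; only the size does.

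**Step 4: one worked case, m = 5% per year, t = 2 years.**
- Standard: 1 − exp(−0.511×2) = 64.0%, against 0.511/0.561 × [1 − exp(−0.561×2)] = 61.4%. Excess 2.6 points.
- Advanced: 1 − exp(−0.357×2) = 51.0%, against 0.357/0.407 × [1 − exp(−0.407×2)] = 48.8%. Excess 2.2 points.
- Risk difference: 13.0 points by Kaplan-Meier, 12.6 by cumulative incidence.

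**Step 5: the range.** Excess of 1 minus Kaplan-Meier over cumulative incidence, standard / advanced, in percentage points:

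| Assumed m per year | 1 year | 2 years | 3.5 years |
|---|---|---|---|
| 1% | 0.18 / 0.14 | 0.53 / 0.45 | 1.03 / 0.98 |
| 2% | 0.36 / 0.28 | 1.05 / 0.89 | 2.05 / 1.95 |
| 3% | 0.54 / 0.42 | 1.57 / 1.32 | 3.04 / 2.89 |
| 5% | 0.90 / 0.69 | 2.59 / 2.18 | 4.98 / 4.73 |

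The time points come from the plan: 1 year is where the design difference is stated, 2 years is the stated mean follow-up, and 3.5 years is the longest follow-up under the design (2.5 + 1).

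**Step 6: effect on the comparison.** The change in the risk difference is the standard-arm excess minus the advanced-arm excess. At m = 5% it is 0.21 points at 1 year, 0.41 at 2 years and 0.25 at 3.5 years. It is smaller at lower rates.

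**The case against.** The strongest reply is that the article is a condensed account. Censoring of non-cardiac deaths is inferred rather than written, and an analysis plan that is not shown could add cumulative incidence curves. Part of this stands: such a plan may already settle the matter. But the article does more than leave a gap. It names both the estimator and the endpoint, and for absolute risk the two do not fit.

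It is also fair to say that the article promises only a comparison of curves by the log-rank test, with no stated risk or risk difference. That limits the point to whatever is read or reported from the curves. The size rests wholly on an assumed rate. The exclusion of severe conditions that would preclude revascularization should lower that rate, the excess is under 1 point at 1 year, and only the first patients enrolled reach 3.5 years. All of this stands and is why the point is minor.

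Four stronger readings are tempting, and the document does not support them:
- *The primary test is invalid.* It is not. With non-cardiac deaths censored, the log-rank test and the Cox model compare the cause-specific hazard of the composite, which is a legitimate comparison.
- *The error carries into the decision model.* The Economic evaluation section names resource use and utility values as data. It does not say that event probabilities come from these curves.
- *One strategy may shift deaths into the non-cardiac category unseen.* This is possible in principle, but nothing in the article indicates it. It would also be a complaint about the endpoint rather than about Kaplan-Meier. Tabulating deaths by arm would answer it.
- *The remedy needs no new data.* This is doubtful. Under Subject evaluation, the records query for patients who cannot be reached at the final assessment lists cardiac death as its only category of death.

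**Conclusion.** The point holds as a low-cost improvement to how absolute risk is presented. Kaplan-Meier curves for this cardiac-only composite would overstate event risk in both arms. At an assumed non-cardiac death rate of 1% to 5% per year, constant and equal between arms, and with the plan's own hazards, the excess is about 0.1 to 0.9 points at 1 year, 0.4 to 2.6 at 2 years and 1.0 to 5.0 at 3.5 years. The between-arm risk difference moves by under 0.5 points. A higher death rate would enlarge these figures, and unequal rates could change the effect on the risk difference; the article has no data on either. The primary test, the adjusted model and the sample size of 495 need no change on this account.

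**What to change.** Keep the log-rank test and the Cox model, and label them as the comparison of cause-specific hazards, with non-cardiac deaths before a first event censored. Present Aalen-Johansen cumulative incidence curves by arm with non-cardiac death as a competing event, and take any reported absolute risks from those curves. Tabulate non-cardiac and all-cause deaths by arm beside them.

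The analysis cost is small. On the data side, the records query under Subject evaluation should also capture non-cardiac death and its date. The Trial status section puts enrolment at 20% of the planned total at the time of writing, so at that stage the query could be widened before most follow-up has taken place.

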### Blinding

The study is not blinded given the nature and purpose of the interventions. Knowledge of imaging results and potential gained from the intervention will need to be considered to implement the appropriate treatment strategy. Therefore, performance bias (that is, systematic differences between groups in the care provided or exposure to factors other than the interventions of interest) and attrition bias (that is, systematic differences between groups in withdrawals from the study) may occur. Detection bias is still a potential concern, but an independent assessor will evaluate the objectively defined primary outcome and an adjudication committee will independently review and adjudicate each clinical event blinded to treatment randomization.

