### Subject evaluation

At baseline, demographic and clinical data will be collected from all participants on standardized case report forms. These data will be collected from the most recent, routine history and physical examination that has been completed by the treating physician. Quality of life questionnaires (EuroQol and Minnesota Living with Heart Failure) will be administered. In addition, the above-mentioned laboratory samples will be collected. To address a secondary objective, whenever possible, an echocardiogram will be performed if LV ejection fraction has not been determined by echocardiography within 6 months prior to randomization. As much as possible, imaging procedures will be performed within 4 weeks after entry into the trial. Subsequent telephone follow-up and repeat blood work will be performed on a predetermined schedule (Table 2). If the patient cannot be reached by telephone for their final assessment, a query will be made at government or national health care resources to verify if any corresponding events have occurred since the last visit (search of corresponding codes for cardiac death, MI, cardiac arrest and cardiac re-hospitalization for WHF, ACS, or arrhythmia). A follow-up echocardiogram will be requested at one year (LV remodeling, LVEF). Within 3 months of the baseline scan the treating physician will be asked to record the HF management plan.

**Table 2 T2:** Patient assessment schedule

	**Baseline**	**3 months**	**6 months**	**12 months**	**18 months**	**24 months**	**36 months**	**48 months**
Imaging (SPECT, PET or CMR)	x							
Blood work	x			x				
Demographic and history	x							
Clinical data collected	x			x				
EuroQol questionnaire	x	x	x	x	x	x	x	x
MLWHF questionnaire	x	x	x	x	x	x	x	x
Telephone follow-up		x	x	x	x	x	x	x

*CMR* cardiac magnetic resonance, *MLWHF* Minnesota Living with Heart Failure, *PET* positron emission tomography, *SPECT* single photon emission computed tomography.

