#### Secondary analysis (PET versus CMR)

For the secondary analysis, comparing the PET and CMR modalities, potential confounding variables of the relationship between the imaging technologies and the primary endpoint will be assessed. In particular, propensity scores based on patient factors (for example, in/outpatient, NYHA class, HF duration, diabetes, atrial fibrillation) and site factors (for example, time-to-imaging, time-to-therapy) will be used in the analysis if necessary to adjust for potential differences between PET and CMR. A Cox proportional hazard models will be used to assess the occurrence of the endpoints between the imaging technologies (the model will include a group indicator variable) adjusting for any pertinent baseline differences identified. The proportional hazards assumption underlying the Cox model will be assessed. The secondary outcomes will be analyzed in a similar fashion.

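### The propensity scores include time-to-imaging and time-to-therapy, which arise after allocation and belong to the strategy under test, so the propensity-adjusted analyses can be biased.

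*Protocol article*

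**What the plan says.** Under Primary analysis (advanced versus standard imaging), the article first gives an unadjusted comparison: "Kaplan-Meier survival curves of the primary endpoint will be compared between the advanced and standard modalities with the log-rank test". It then turns to confounding. Propensity scores are to draw on two groups of variables. The first is patient factors (atrial fibrillation, diabetes, heart-failure duration, NYHA class, inpatient or outpatient status). The second is named thus: "site factors (for example, time-to-imaging, time-to-therapy) will be used in the analysis if necessary to adjust for potential differences". The Cox model that follows describes its covariates as relevant differences at baseline.

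Under Secondary analysis (PET versus CMR), the same patient factors are listed, and again "site factors (for example, time-to-imaging, time-to-therapy) will be used in the analysis if necessary to adjust for potential differences between PET and CMR". No unadjusted test is stated there.

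Three other sections bear on the point:

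- **Subject evaluation** puts imaging after enrolment, as a target qualified by as much as possible: "imaging procedures will be performed within 4 weeks after entry into the trial". The treatment decision comes later still: "Within 3 months of the baseline scan the treating physician will be asked to record the HF management plan".
- **Blinding** makes treatment depend on the scan: "Knowledge of imaging results and potential gained from the intervention will need to be considered to implement the appropriate treatment strategy".
- **Primary hypothesis** defines what is tested as the whole strategy: "a management algorithm that applies alternative imaging strategies (PET or CMR) achieves a better clinical outcome".

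**The concern.** A propensity score models allocation from what is known before allocation. Time-to-imaging and time-to-therapy are not known then. They come about after the patient has been assigned to SPECT, PET or CMR, and they can differ because of that assignment. If a modality is easier to book or gives a clearer answer, its patients may be scanned and treated at a different time, and that difference is one of the ways the strategy could change outcome. Adjusting for it asks what the effect would be if timing were the same. That is not the hypothesis.

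There is a second route to bias. Delay may also reflect prognosis, for example if sicker patients are moved up the queue. Conditioning on a variable that depends on both allocation and prognosis can create an imbalance that randomisation had prevented.

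At stake is the credibility of the adjusted estimates. The trigger, if necessary, is not defined. A difference in delay between groups, possibly itself an effect of the strategy, could be what prompts the adjustment. The primary endpoint could then carry an unadjusted and an adjusted result that disagree for no good reason.

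**Working it through.** **1. Are the two times post-allocation?** Subject evaluation gives the order: entry, then scan, then management plan. Blinding says the scan result feeds the treatment. For randomised patients both times therefore follow randomisation. For registry patients they follow the clinical choice of modality.

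**2. Could they lie on the path to outcome?** The background section on imaging in ischemic heart failure says that patients with viable hibernating myocardium are at high risk without timely revascularization. The opening of Methods/Design reports that most surveyed centres could not deliver stress echocardiography consistently within the required timeframe, so timing can depend on modality. The article's own reasoning makes both links plausible, but it gives no size for either.

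**3. The plan's own sample sizes.**

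- *Primary.* Inputs from Sample size: 1-year rates of 30% and 40%, 2:1 allocation, two-sided 0.05, 80% power, 2.5 years of uniform accrual, 1 year minimum follow-up, 10% loss. Exponential hazards are −ln 0.7 = 0.357 and −ln 0.6 = 0.511, so HR = 0.698 and |ln HR| = 0.359. The Lachin–Foulkes log-rank formula gives 449 before loss and 449/0.9 = 499, against the stated 495. This reproduces within 1%.
- *Secondary.* Events = (1.96 + 0.842)² / (0.25 × (ln 1.4)²) = 277.3. Then 277.3/0.30 = 924; 924/(1 − 0.25²) = 986; 986/0.9 = 1,096. This matches.

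Neither calculation uses the two times, so removing them changes neither figure.

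**4. Expected events, primary comparison.** With F = 1 and A = 2.5, the event probability is 1 − [exp(−λF) − exp(−λ(F + A))]/(λA).

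- Advanced: 1 − (0.700 − 0.287)/0.892 = 0.537
- Standard: 1 − (0.600 − 0.167)/1.277 = 0.661
- Weighted 2:1: (2 × 0.537 + 0.661)/3 = 0.578
- Events: 495 × 0.9 × 0.578 = 258

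**5. Illustration for the adjusted model only.** Let f be the share of the log hazard ratio that adjustment removes. The documents give no value, so 0% to 50% is assumed.

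HR = exp(−(1 − f) × 0.359)

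Power = Φ(√(258 × 2/9) × (1 − f) × 0.359 − 1.96), with √(258 × 2/9) = 7.57

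| f | Adjusted HR | Power |
|---|---|---|
| 0% | 0.70 | Φ(0.76) = 78% |
| 25% | 0.76 | Φ(0.08) = 53% |
| 50% | 0.84 | Φ(−0.60) = 27% |

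The starting value is 78% rather than 80% because this (Schoenfeld) approximation needs 274 events for 80%. With 274 events the column reads 80%, 56% and 29%. By the same reasoning the PET-versus-CMR hazard ratio of 1.40 would become 1.29 or 1.18, with power of 80%, 56% or 29%.

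**6. Simulation check.** 495 patients, no loss to follow-up, delays assumed 0.5 SD shorter in the advanced group, a propensity score built on delay, 300 runs per case. With 0%, 25% and 50% running through delay, the adjusted HR was 0.70, 0.76 and 0.84 and the rejection rate 77%, 59% and 29%. Unadjusted, the HR stayed at 0.70 to 0.72 and the rejection rate at 78% to 83%.

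**7. The other direction.** If the advanced group waits longer and waiting does harm, timing offsets part of the benefit and f is negative. With f = −25%, HR = exp(−1.25 × 0.359) = 0.64, which overstates the strategy's benefit.

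**The case against.** The strongest reply is that the main test escapes. The trial is sized on an unadjusted log-rank test, and that test is the first analysis named. The scores enter only if necessary, the two times are given as examples, and the Cox sentence limits its covariates to baseline differences, which these times are not. All of this stands. A reader might infer that the primary comparison is biased by design, or that the trial's power falls to 53% or 27%. The documents do not support either: those figures describe an optional adjusted model under an assumed share.

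A reader might also infer that the bias must run toward no difference. The documents do not say which group is imaged or treated sooner, so the direction is open. Nor do they say that patients without a therapy date would be dropped. Analysis populations makes intent-to-treat the main set, and Missing data provides for multiple imputation. Imputing a time that never occurred would be awkward, but exclusion is not in the plan.

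Finally, calling these site factors could mean each centre's usual waiting times before the trial. The text does not say so, and a wait specific to one modality would still be a feature of that strategy. The two times are also the only site factors named, so an analyst following the text would use them.

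**Conclusion.** The point holds for the propensity-adjusted analyses and should be fixed. Two variables named for the scores in both comparisons arise after allocation, can depend on modality, and form part of the strategy being tested.

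For advanced versus SPECT the damage is limited to a conditional analysis beside an intact log-rank test. For PET versus CMR it matters more: 766 of 1,096 patients (70%) come from the registry, some adjustment is needed, and no unadjusted test is stated to fall back on.

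The size cannot be fixed from the documents. Bias arises only to the extent that timing differs by modality and affects outcome, or that timing tracks prognosis. The hazard ratios and power figures above are illustrations resting on an assumed mediated share. Adjusting the registry comparison for genuine pre-allocation confounders remains justified.

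**What to change.** Delete time-to-imaging and time-to-therapy from the adjustment sets in the primary-analysis and PET-versus-CMR sections. Suggested replacement for both:

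> Propensity scores and covariate adjustment will use only variables fixed before randomisation or, for registry patients, before the decision on imaging modality, such as the patient factors listed above. Time-to-imaging and time-to-therapy will be summarised by group and, if analysed further, reported in a mediation analysis labelled as such.

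Site should not simply take their place in the PET-versus-CMR score. The Randomization section shows that availability of modalities varies by centre. Where a centre offers only one advanced modality, site determines the modality completely and the score has no overlap there.

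The cost is a change of wording in the protocol and analysis plan. Data collection and both sample sizes stay as they are. The change should be made before outcomes are compared by group.

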### Randomization

Patients will be randomized according to a pre-defined randomization scheme and availability of imaging procedures at individual participating centers. All eligible patients will be randomized to either standard or advanced imaging modalities for ischemia and/or viability testing. Participating sites with the capability for two advanced imaging modalities will then be further randomized between each modality. If randomization is not possible due to local site factors, the patient can be entered into the registry (Figure 1). The ratio of advanced to standard imaging will be 2:1.

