#### Secondary outcomes

For the secondary outcomes PCI, CABG, HF symptoms and NYHA class, chi-square tests will be used to compare the advanced and standard imaging technologies; logistic regression analysis will be used for adjusting any pertinent baseline differences identified. For the secondary outcomes LVEF, MLHFQ and EQ5D, analysis of variance will be used to compare trends over time between the advanced and standard technologies. Analysis of covariance will be used for adjusting any pertinent baseline differences identified.

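### The adjusted models choose covariates from observed baseline differences rather than from a fixed prognostic set, which forgoes precision and leaves the choice open after the arms are compared

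*Protocol article*

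**What the plan says.** All references are to the protocol article.

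- **Sample size** sizes the primary comparison "using the two-sided log-rank test for comparing advanced (PET + CMR) versus standard modalities with a 2:1 patient allocation" and arrives at "a sample size of 495 patients (of which 330 are allocated to the advance modality and 165 are allocated to the standard modality").
- **Primary analysis** states: "Kaplan-Meier survival curves of the primary endpoint will be compared between the advanced and standard modalities with the log-rank test". It then adds a Cox model "adjusting for any pertinent baseline differences identified". Propensity scores are conditional on being needed, and their factors are given only as examples. The patient factors are in/outpatient status, NYHA class, HF duration, diabetes and atrial fibrillation; the site factors are time-to-imaging and time-to-therapy.
- **Secondary outcomes** uses chi-square tests and analysis of variance first. Logistic regression then adjusts for differences found, and "Analysis of covariance will be used for adjusting any pertinent baseline differences identified".
- **Secondary analysis (PET versus CMR)** repeats the Cox and propensity rule.
- The opening paragraph of **Statistical analysis** says how differences are found: patient characteristics are summarised by imaging technology and the differences are reviewed for clinical significance.
- **Blinding** says the study is open.
- **Randomization** gives a single 2:1 ratio and says: "Patients will be randomized according to a pre-defined randomization scheme and availability of imaging procedures at individual participating centers".
- **Registry** says advanced-imaging registry patients count in the sample size and data analysis, and excludes only SPECT registry patients from the primary analysis.
- **Missing data** plans MMRM for continuous outcomes measured repeatedly.

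**The concern.** The article does more than leave a covariate list to the analysis plan. It states a rule for building the list, and the rule is a poor one.

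Between randomised arms, a baseline difference is chance. A covariate earns its place by predicting outcome, whether or not it differs between arms. Under the stated rule a strong but balanced predictor is omitted, so the precision it would have bought is given up. Neither which differences count as pertinent nor when a propensity score is needed is defined, and both are decided after the groups have been compared in an open trial.

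Two of the propensity examples raise a further problem. Imaging is done after trial entry (Subject evaluation), so at patient level time-to-imaging and time-to-therapy arise after randomisation. They may be affected by the assigned strategy, and adjusting for them could remove part of the effect under study.

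**Working it through.** **1. Reproduce the planned size.** Inputs from Sample size: 30% versus 40% at 1 year, 2:1, two-sided 0.05, 80% power, 2.5 years uniform accrual, 1 year minimum follow-up, 10% loss.

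- Exponential hazards: advanced −ln 0.70 = 0.3567; standard −ln 0.60 = 0.5108; HR = 0.3567/0.5108 = 0.698.
- Event probability over the design, P = 1 − [e^(−λ) − e^(−3.5λ)]/(2.5λ): 0.5368 and 0.6612, averaging 0.5783 at 2:1.
- Lachin-Foulkes, with φ(λ) = λ²/P and mean hazard 0.4081: φ = 0.2855 (mean), 0.2370 (advanced), 0.3947 (standard).
- N = [1.96√(0.2855 × 4.5) + 0.8416√(0.2370 × 1.5 + 0.3947 × 3)]² / (0.5108 − 0.3567)² ≈ 448.9.
- 448.9/0.90 = 499. With 10% per year exponential loss instead, the result is 496. The article has 495, so the figure stands.
- Other event formulas bracket it: Freedman 476, Schoenfeld 527.

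For PET versus CMR: events = (1.96 + 0.8416)²/[0.25 × (ln 1.4)² × (1 − 0.25²)] = 295.8, and 295.8/0.30/0.90 = 1,096, an exact match.

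**2. Power under three covariate rules.** Simulation at 495 × 0.9 = 446 evaluable patients, 3,000 runs per row (simulation error about √(0.8 × 0.2/3000) = 0.7 points). The unadjusted HR is held near 0.698, because the article's 30% and 40% are marginal rates. The SD of the prognostic score on the log hazard is assumed. So is the threshold for calling a covariate imbalanced, since the article defines none.

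| SD | Unadjusted | Imbalance-chosen | Prespecified |
|---|---|---|---|
| 0.3 | 79.1% | 79.6% | 82.2% |
| 0.5 | 79.7% | 80.8% | 85.7% |
| 0.8 | 79.5% | 81.9% | 92.5% |
| 1.0 | 79.1% | 82.2% | 96.2% |

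The gain over unadjusted is 3.1, 6.0, 13.0 and 17.1 points with a prespecified set. Under the imbalance rule it is 0.5, 1.1, 2.4 and 3.1 points.

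**3. Type I error.** With five prognostic covariates, adjusting only for those imbalanced at p < 0.10, null rejection was 0.041 (SD 0.5) and 0.046 (SD 0.7). It rises to about 0.06-0.09 only if the best of the unadjusted, imbalance-adjusted and fully adjusted results is reported.

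**4. Site capability.** Two equal strata, 2:1 in both, 4,000 runs. For stratum hazards differing 1, 1.3, 1.5, 2 and 3-fold:

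- unstratified log-rank: 78.8, 79.1, 77.8, 75.6 and 67.8%
- stratified log-rank: 79.0, 79.4, 78.8, 79.4 and 78.5%

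The cost of not stratifying is at most 1 point up to 1.5-fold, about 4 points at 2-fold and about 11 at 3-fold.

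**The case against.** The strongest reply is that the primary test involves no covariate choice. The log-rank is named in both the sample size and the analysis sections, so the rule touches only supporting models. The full analysis plan, not shown, may list the covariates, and five plausible ones already appear as propensity examples. This limits the consequence, but the article still states an imbalance criterion where it could have stated a prognostic one.

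Four stronger readings are tempting, and the documents do not support them:

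- **The trial is underpowered.** It is not: 495 was set for an unadjusted test and reproduces. Unadjusted power falls below 80% in simulations that calibrate the hazards differently, not against the article's own marginal rates. The gain in the table is relative to a better analysis.
- **The rule inflates false positives.** Applied as written it does not (step 3). Inflation needs someone to pick among results, and the article contains no such rule. The defect is undefined discretion.
- **Ignoring site capability biases the primary test.** That would need the allocation ratio to differ between site types. With an assumed 1:1 versus 4:1, null rejection of the unstratified test is 10% at a 1.3-fold stratum hazard ratio and 42% at 2-fold. The article gives one ratio, 2:1, and uses capability to decide the further PET/CMR randomisation. It also does not say that the log-rank is unstratified, and the figure of the scheme is not shown.
- **All baseline differences are chance.** This holds only among randomised patients. Registry leaves it unclear whether advanced-registry patients enter the primary comparison, although Sample size rests that comparison on 495 allocated patients and brings the registry in for PET versus CMR. PET versus CMR pools registry patients and does need confounding adjustment.

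Nor are analysis of variance and covariance the whole plan for continuous outcomes, since MMRM is also planned. Whether the baseline value enters that model is not stated.

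**Conclusion.** The point holds for the adjusted Cox, logistic and covariance analyses. Selecting covariates by observed imbalance recovers little of the precision on offer (0.5 to 3.1 points of power, against 3.1 to 17.1 with a prespecified set) and leaves the model open until the arms have been compared. The direction is secure. The size depends on the assumed prognostic SD of 0.3 to 1.0, exponential survival, and covariates that are collected and carry that prognostic information.

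The log-rank is valid and the 80% claim stands. Stratification by site capability is a small matter unless stratum hazards differ about 2-fold or more, provided 2:1 holds at every site. The change should be made, but the primary test does not fail without it.

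**What to change.** 1. In Primary analysis and Secondary outcomes, replace the clause on differences identified with a fixed set of prognostic baseline covariates, always used. For example: NYHA class, LVEF, diabetes, atrial fibrillation, HF duration, in/outpatient status and eGFR. About 446 × 0.578 = 258 events are expected, enough for seven covariates. State that the adjusted hazard ratio is conditional on these and supports the log-rank.
2. Include the baseline value in the covariance model or MMRM for LVEF, MLHFQ and EQ5D whether or not the arms differ. Baseline echocardiography is done only where possible, so say how a missing baseline LVEF is handled.
3. State that advanced versus standard uses randomised patients only, and reconcile Registry with this. Drop the propensity score from that comparison, including time-to-imaging and time-to-therapy.
4. For PET versus CMR, keep the confounding adjustment but fix its covariates before outcomes by group are seen. Its sample size already presumes an identified set.
5. Optionally, stratify the log-rank and Cox by site imaging capability (PET only, CMR only, both).

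The cost is wording. The example covariates are named in the article, needed for eligibility, or derivable from the creatinine measured at randomisation; confirm that each is on the case report form. No patients or visits are added.
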